#### Outcomes

For MSM, we will assess important baseline characteristics for describing the sample, including: age, income, gender, education, ethnicity, relationship status, religion, sexual identity, sexual practices, HIV knowledge, HIV testing readiness, HIV testing history and histories of experiencing intersecting stigmas, access and utilization of health and social services, civic engagement and neighborhood. For HCF staff, we will assess a more limited set of baseline characteristics. Our primary outcome will be an uptake of HIV testing within six months of randomization. We will also record the frequency of HIV testing within six months, but we anticipate that few participants will take more than 1 test in this short period. Our secondary outcome will be a reduction in intersectional stigma, both at the HCF-level and among MSM participants. For HCFs, we will construct a latent variable of intersectional stigma using items from questionnaires that measure HIV stigma and discrimination and LGBT stigma among health facility staff. For intersectional stigma among MSM, we will also create a latent variable that is drawn from three scales that measure HIV stigma, same-sex stigma, and gender non-conforming stigma. Outcomes will be assessed within 3-and 6-months post-intervention for HCFs and 3- and 6-months post-intervention for MSM.

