#### Step 8 (Test)

We will conduct an RCT of the multi-level intervention with a 6-month wait-list control. In each city, we will create two pairs from the 4 HCF sites matched by the number of HIV tests performed in the calendar year 2020. We will randomly assign clinics (enveloped odd/even) within each pair to either receive the HP+ or the wait-list control. MSM will be randomly assigned to receive either Nyansapo and HIVE^3^ or wait-list control. MSM in the intervention group will be asked to follow-up for HIV testing and services at one of the HCFs assigned to the HP+ intervention and the MSM in the wait-list control group will be asked to follow-up at any of the HCFs in wait-list control. Nurses from the intervention HCFs will participate as guest facilitators in one of the Nyansapo sessions and will use that opportunity to reach out to MSM to visit their facility for testing. Our primary hypothesis is that the multi-level intervention will increase uptake of HIV testing among MSM participants. We will use research data collectors to measure frequency of HIV testing among MSM at 3- and 6-months post-intervention using a combination of self-report survey and verification by study nurses (for men who get tested for HIV at participating HCFs.) Our secondary hypothesis is that the multi-level intervention will reduce intersectional stigma that HCF staff convey and that MSM experience in HCFs. We will use research data collectors to administer a survey measuring intersectional stigma 1) in the HCFs at baseline, 3-months post and 6-months post intervention and 2) among MSM at baseline, 3- and 6-months post intervention.

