Additionally, multivariable logistic regression will be used to compute the adjusted odds ratio and 95% CI for the binary outcome–HIV testing. The successful uptake of HIV testing can be dependent on the environment in the HCF so that HIV testing among MSM participants at the same HCF may be corrected or “clustered.” To account for the potential post-randomization clustering effect in this individually randomized clinical trial, a generalized linear mixed-effects model with a logit link function will be fitted, and this model includes both HCF cluster-level and MSM individual-level factors. Structural equation modeling will be performed to evaluate the association between the multilevel intervention and uptake of HIV testing while simultaneously assessing the mediation role of intersectional stigma. We will also perform the same analyses for HIV testing within three months of randomization, although the analyses may be underpowered. The likelihood of intervention contamination across the study groups could not be excluded, because some participants may not receive the respective interventions to which they are randomized, e.g., some members of the control group may seek health care at the intervention HCFs during this trial. Therefore, we will also perform per-protocol analysis, which includes only those participants who strictly adhere to the protocol and report the results along with the results of the intention-to-treat analyses. To estimate the effect size of the HP+ intervention for staff, we will compare the rates of willingness to provide healthcare to MSM between the staff in intervention and control HCFs. Chi-square test and t-test will be used for the binary (willingness) and continuous (stigma score) outcomes, respectively. Multivariate logistic or linear regression models will be fitted while adjusting for confounding factors such as sex and job title of the staff.

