The two MSM-led organizations will provide recruitment, data collection and retention services for MSM in the study. Research assistants will recruit, obtain informed consent, collect data, and follow-up with participants to support study retention. The research assistant will record all client contact information in an online data management information system via computer tablets. We will recommend that participants complete the informed consent and survey procedures inside of our partner’s data collection sites. Survey procedures will include coming to a data collection site and completing the survey using a tablet. No paper data will be collected and data will be automatically stored in the online data collection system. If a participant prefers, a study staff member can read the questions to the participant and document the participant’s answers.

Permission to collect HIV testing data will be requested in the informed consent form. We will also ask for participants to complete an authorization for medical records release. For those who report a post- intervention HIV test, we will seek to get confirmation from the HCF that test was conducted and the test result. For participants who report HIV testing at their assigned HCF, the study nurse will verify study participants’ name against the HCFs HIV test log to confirm the test was done at the facility. The study nurse will use an internet enabled computer tablet device to record the date of the test and test result directly into the online data management system used in the study.

We will destroy all identifiers after the data analyses have been completed. We define completed as the publication of the results of the primary research questions in a scientific peer-reviewed journal. Before that time, there may arise a need to audit the data to a level that is identifiable. We will maintain the capacity to conduct such a detailed audit until the primary results are published. To maximize participant confidentiality, all data will be identified only by the subject ID number, and no participant names will appear on any research materials. All research data will be maintained on a secure computer system with actively maintained high level of security to ensure the confidentiality of our databases. Access to the list containing participant IDs will only be provided on a need-to-know basis to approved study staff.

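### The planned mediation model uses a stigma score taken after many or all of the HIV tests it is meant to explain, so its result is association rather than mediation

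*Protocol article*

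**What the plan says.** The Statistical analysis plan section gives mediation one sentence: structural equation modeling will "evaluate the association between the multilevel intervention and uptake of HIV testing while simultaneously assessing the mediation role of intersectional stigma". It does not name the stigma variable or the survey wave.

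Three other statements fix the timing:

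- **Outcome window.** In Outcomes: "Our primary outcome will be an uptake of HIV testing within six months of randomization". After the mediation sentence, the analysis section adds: "We will also perform the same analyses for HIV testing within three months of randomization".
- **Stigma surveys.** Step 8 (Test) places them "among MSM at baseline, 3- and 6-months post intervention", and for staff "in the HCFs at baseline, 3-months post and 6-months post intervention". There are two post-baseline waves.
- **Test dates.** For tests at the assigned facility, the study nurse will "record the date of the test and test result directly into the online data management system" (Confidentiality and security of data).

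Step 8 also describes the stigma to be changed. The secondary hypothesis is that the intervention will "reduce intersectional stigma that HCF staff convey and that MSM experience in HCFs".

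**The concern.** A mediator has to come before the outcome it explains. Here the outcome accumulates from randomization, while the mediator is first measured about three months after the intervention. A man who tests early has his outcome settled before his stigma is scored.

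The order matters because the reverse path is plausible. An HIV test is a visit to a health care facility, and stigma met in facilities is part of what the trial aims to change, so the visit may alter what a man later reports. Early tests are likely: Step 8 has nurses from intervention facilities join a Nyansapo session and invite men to come for testing. More men are expected to test in the intervention arm, so any effect of testing on stigma also produces a difference in stigma between arms. The model cannot tell this pattern from stigma acting on testing.

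At stake is how the mechanism is interpreted. The introduction presents stigma as a barrier to testing, and a positive mediation result would be read as support for that.

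**Working it through.** **Step 1. Time order.** Baseline stigma precedes the intervention and cannot mediate it, so the mediator must come from a later wave.

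| Outcome window (from randomization) | 3-month stigma score | 6-month stigma score |
|---|---|---|
| Six months | after all tests in the first three months | at or after the end of the window |
| Three months | at or after the end of the window | after the window |

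The windows run from randomization and the surveys from the intervention, so any wait for a retreat places the scores later still. No cell has the mediator wholly before the outcome. The three-month repeat is the clearest case, on the reading that the same analyses include the structural equation model.

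**Step 2. Inputs for the size.** The protocol gives no figure for mediation to reproduce. From its Sample size section: testing 40% v 70%, 86 evaluable men per arm. Assumed, with no support in the document:

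- true effect of stigma on testing: zero
- a, direct fall in stigma from the intervention: 0.3 SD
- d, fall in reported stigma after a testing visit: 0.1 to 0.5 SD
- share of tests before the 3-month survey: 60%

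Mediation is declared when the arm-to-stigma and stigma-to-testing paths are both significant at 5%.

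**Step 3. Check by hand, all tests before the score, d = 0.5 SD.**

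- Arm-to-stigma path: a + d × (0.70 − 0.40) = 0.3 + 0.15 = 0.45 SD. Standard error √(2/86) = 0.1525, so z = 2.95 and the chance of significance is about 84%.
- Stigma-to-testing path: in a logit model with arm, the apparent coefficient is d = 0.5 per SD. Standard error 1/√[86 × (0.7×0.3 + 0.4×0.6)] = 1/√38.7 = 0.161, so z = 3.11 and the chance is about 87%.
- Both: 0.84 × 0.87 ≈ 73%.

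With d = 0.3 the same steps give z = 2.56 (73%) and z = 1.87 (46%), so about 33%.

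**Step 4. Simulation.** Ranges cover separate runs with linear and logit outcome models. The truth is no mediation.

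| Effect of a testing visit on reported stigma | 6-month score | 3-month score, six-month outcome |
|---|---|---|
| 0.1 to 0.2 SD fall, both arms | 5% to 16% | 3% to 6% |
| 0.3 SD fall, both arms | 31% to 34% | 11% to 14% |
| 0.5 SD fall, both arms | 70% to 73% | 31% to 33% |
| 0.3 SD fall, intervention arm only | 11% to 12% | 6% to 7% |
| 0.5 SD fall, intervention arm only | 28% to 32% | 11% to 13% |
| 0.3 to 0.5 SD fall in intervention arm, equal rise in control | 1% to 2% | 1% to 2% |
| 0.3 SD fall, both arms, a = 0 | about 4% | about 1% |
| 0.5 SD fall, both arms, a = 0 | 13% to 14% | 2% to 4% |

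With d = 0 and a = 0.3 the rate is 3%, so the excess comes from the reverse path. If 50% rather than 60% of tests are early, the 3-month figures for falls of 0.3 and 0.5 SD in both arms are 8% and 21%.

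**Step 5. Time-ordered model.** When 3-month stigma explains only later tests, false mediation is 1% to 5% in every scenario run.

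**Step 6. Its price.** Expected testers: 86 × 0.70 + 86 × 0.40 = 94.6. With 40% of them late, about 38 of 172 men have a late test. If mediation truly exists (0.3 SD effect on stigma, odds ratio 1.5 to 2 per SD, both assumed), power is about 21% to 44%.

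**The case against.** **The choice of wave and lags belongs in a statistical analysis plan.** This is fair as far as it goes: the article names no wave, and a time-ordered model is itself a structural equation model. But the outcome windows are stated in the article, and neither wave precedes them. The repair has to change the outcome window used for mediation, which goes beyond filling in a detail.

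**The mediator may be staff stigma.** Outcomes defines two latent variables, one for facilities and one for MSM, and the mediation sentence does not choose. One man's test is unlikely to move a score from sampled staff. This stands: the concern applies to MSM-reported stigma and much less to the staff score.

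**The high rates depend on the assumptions.** This also stands. A reader might infer that the model will usually report false mediation. The document gives no size for the reverse effect and no timing of tests. A fall of 0.3 to 0.5 SD after one visit equals or exceeds the direct effect assumed for the whole intervention. If the mechanism is a good experience at a trained facility, the rows limited to the intervention arm fit better, and they are much lower.

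**Mediation is not an objective.** This stands. A reader might take it for one, or infer that the larger trial would be built on a false mechanism. The two aims are feasibility and acceptability, and effect-size estimation. The hypotheses concern testing and stigma reduction, and the Discussion ties the next trial to those results.

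**Conclusion.** The point holds as a minor one. With the windows and survey times the protocol states, no MSM stigma score precedes the whole outcome it is meant to mediate. For the three-month repeat, no post-baseline score precedes the end of the window at all. This follows from the text without assumptions.

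How far it misleads does depend on assumptions. With no true mediation and a 0.3 SD direct effect on stigma, the false-positive rate runs from about nominal to about 70%. The upper end needs a 0.5 SD fall after testing in both arms and the 6-month score. The supported statement is that the model can report mediation where there is none, not that it will.

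A reader might also infer that the trial's main result is at risk. It is not: the primary chi-square test compares testing by assignment and does not use stigma.

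**What to change.** - Take the indirect effect only from 3-month MSM stigma to tests after that survey, with baseline stigma and earlier testing in the model.
- Do not use 6-month stigma as a mediator of testing.
- Report the structural equation results for the cumulative six-month outcome and for the three-month outcome as association, not mediation.
- State whether the mediator is the MSM or the staff stigma variable.
- Place tests in time by the study-nurse date where the test was at the assigned facility. For tests elsewhere, where no recorded date is described, use the survey interval (3- or 6-month) in which the test is first reported.

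This changes the analysis only; no new visit or measurement is needed. The cost is precision. Outcomes expects few men to test more than once, so early testers add little to the later interval. With about 38 late tests under the assumptions above, the indirect effect will be imprecise and should be labelled exploratory. Correct time order also leaves confounding between stigma and testing, because stigma is not randomized.

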## Discussion

This intervention utilizes a multi-level approach to increase HIV testing, and decrease intersectional stigma, experienced by MSM in Ghana. If the intervention is found to be successful, it has the potential to decrease rates of HIV among MSM in Ghana. This trial represents the next step toward this goal. In Aim 1 we will combine three interventions previously found to be efficacious. We will then conduct a waitlist-controlled RCT of the adapted intervention to assess feasibility and acceptability of the intervention. In Aim 2 we will estimate the effect size of the intervention on HIV testing and intersectional stigma reduction. At the end of this trial, we will have sufficient data to conduct a larger efficacy/effectiveness trial of the multi-level intervention.

This study has significant potential benefits to the scientific community and communities of healthcare workers and key populations, such as MSM. The study will generate knowledge that will be used to inform the development of intervention protocols that can help reduce intersectional stigma among HCF staff and MSM. These reductions in stigma can improve HIV testing and service engagement for prevention and treatment (including, but not limited to, HIV). Furthermore, this study will contribute to further development of the HIV implementation science program, which aims to make scientific advances through research while simultaneously making gains and improvements in HIV for key populations in real-world clinical practice environments.

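### Stigma among MSM is a secondary outcome with no declared arm comparison, and the only stated use of baseline data depends on a balance check and is less precise than routine baseline adjustment

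*Protocol article*

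**What the plan says.** All of this is in the protocol article.

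- **Outcome.** Outcomes section: "Our secondary outcome will be a reduction in intersectional stigma, both at the HCF-level and among MSM participants". For the men, "we will also create a latent variable that is drawn from three scales", covering HIV, same-sex and gender non-conforming stigma.
- **Hypothesis and timing.** Step 8 (Test): "Our secondary hypothesis is that the multi-level intervention will reduce intersectional stigma that HCF staff convey and that MSM experience in HCFs". The survey is given "among MSM at baseline, 3- and 6-months post intervention".
- **Aim.** Discussion: "In Aim 2 we will estimate the effect size of the intervention on HIV testing and intersectional stigma reduction".
- **Staff analysis.** Statistical analysis plan: "Chi-square test and t-test will be used for the binary (willingness) and continuous (stigma score) outcomes, respectively". This sentence belongs to a block that opens with the effect of the facility training on staff. The regressions that follow adjust for staff characteristics such as sex and job title.
- **Analysis that could reach MSM stigma.** The same section describes a structural equation model relating the intervention to uptake of testing "while simultaneously assessing the mediation role of intersectional stigma". It does not say whether the mediator is the men's stigma or the facility's, and it lists no covariates.
- **Use of baseline data.** The same section starts by comparing the arms at baseline. Variables found non-equivalent are then handled by difference in differences. Nothing is said about baseline values when the arms are judged equivalent.

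**The concern.** The analysis section is specific about other outcomes. It names a chi-square test, logistic regression and a mixed model for testing uptake, and a t-test and linear regression for the staff stigma score. The men's half of the same secondary outcome has no declared estimate, main visit or covariates.

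Two things are at stake.

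1. The study is meant to supply effect sizes for a larger trial. If the MSM stigma effect is not fixed in advance, it could be taken after the data are seen from the mediation-model path, a follow-up comparison, a change score or a conditional difference in differences. These can give different answers.
2. The one baseline rule that is stated is a weak choice. A pre-specified adjustment for a score already being collected is more precise than either branch of that rule, and it does not depend on a preliminary check.

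**Working it through.** **Is any direct arm comparison of MSM stigma stated?** Going through the Statistical analysis plan section in order:

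| Analysis | Target |
|---|---|
| Proportions with CI, chi-square, logistic regression, mixed model | HIV testing among MSM |
| Structural equation model | HIV testing, with stigma (whose is not stated) as mediator |
| Chi-square, t-test, logistic and linear regression | Staff willingness and staff stigma score |

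Only the structural equation model can reach MSM stigma. Its intervention-to-stigma path is not named as the test of the secondary hypothesis.

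**Inputs for the size**

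- 86 men per arm at 6 months (Sample size section), and 216 recruited, so 108 per arm if split equally.
- The plan gives no figure for MSM stigma, so there is none to reproduce.
- Correlation r between baseline and follow-up stigma: not given; 0.3, 0.5 and 0.7 are assumed.
- Also assumed: equal variance at baseline and follow-up, two-sided 5% level, 80% power, one follow-up visit.

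**Relative variance of the arm difference** (follow-up-only comparison = 1)

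- Baseline adjustment: 1 − r²
- Difference in differences (change score): 2(1 − r)
- Adjustment relative to difference in differences: (1 − r²) / [2(1 − r)] = (1 + r)/2

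| r | Adjusted | Diff-in-diff | Cut vs follow-up only | Cut vs diff-in-diff |
|---|---|---|---|---|
| 0.3 | 0.91 | 1.40 | 9% | 1 − 0.65 = 35% |
| 0.5 | 0.75 | 1.00 | 25% | 1 − 0.75 = 25% |
| 0.7 | 0.51 | 0.60 | 49% | 1 − 0.85 = 15% |

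Below r = 0.5, difference in differences is less precise than ignoring baseline.

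**Detectable difference without clustering.** Follow-up only: (1.960 + 0.842) × √(2/86) = 0.427 SD. Multiply by √(1 − r²) for adjustment and by √(2(1 − r)) for difference in differences. The last two columns give power for an assumed true effect of 0.4 SD, for which follow-up only has 74.6%.

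| r | Adjusted | Diff-in-diff | Power, adjusted | Power, diff-in-diff |
|---|---|---|---|---|
| 0.3 | 0.408 SD | 0.506 SD | 78.5% | 60.1% |
| 0.5 | 0.370 SD | 0.427 SD | 85.7% | 74.6% |
| 0.7 | 0.305 SD | 0.331 SD | 95.7% | 92.3% |

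**With clustering.** Suppose the plan's ICC of 0.10 for testing also held for stigma, with 86/4 = 21.5 men per facility. The design effect is 1 + 20.5 × 0.10 = 3.05. The detectable differences become 0.746 SD for follow-up only, 0.712 / 0.646 / 0.533 SD adjusted, and 0.883 / 0.746 / 0.578 SD for difference in differences. The ranking is unchanged.

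**Effect of a chance imbalance.** With 108 per arm, the standard error of the baseline difference is √(2/108) = 0.136 SD. A difference beyond 0.2 SD in either direction then has probability of about 0.14. Given an imbalance of 0.2 SD and an assumed r = 0.6, a follow-up-only comparison carries 0.6 × 0.2 = 0.12 SD of it into the effect. Difference in differences subtracts the full 0.20 and leaves 0.12 − 0.20 = −0.08 SD. Linear baseline adjustment removes it in expectation.

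**The case against.** The case against has real substance.

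- **Baseline stigma is ignored.** A reader might infer this, but the documents do not support it. The sentence on the structural equation model neither includes nor excludes covariates, and a condensed article may leave them to a fuller plan. The difference-in-differences provision is a stated, if conditional, use of baseline data.
- **No arm comparison is possible.** This also goes too far. Arm is randomised, so the intervention-to-stigma path is itself an arm contrast, and such a model suits an outcome defined as a latent variable. What can be said is that the path is not declared as the estimate for the secondary hypothesis.
- **The largest gain always applies.** At r = 0.7, adjustment is worth 1/0.51, or 96% more men, but only against a follow-up-only comparison, to which the plan does not commit. Against difference in differences the same r gives 0.60/0.51, about 18%.
- **The stakes are modest.** This is a secondary outcome in a study meant to provide preliminary data, and no confirmatory claim rests on it.
- **The remedy has limits.** No randomisation strata for MSM are stated. Control men may use any control facility and some men may attend none, so a facility term may be undefined for some.

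These points narrow the criticism and shape the fix. They do not answer the remaining point: the one baseline rule that is written down is conditional and less efficient, and the direct stigma-score comparison is written for staff only.

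**Conclusion.** The point holds in a limited form. MSM stigma is a secondary outcome and hypothesis and part of Aim 2, yet the analysis section declares no between-arm estimate for it. Its only baseline rule makes the choice of estimator depend on an equivalence check. Adjusting for baseline in every case reduces variance by 9% to 49% against a follow-up-only comparison and by 35% to 15% against difference in differences, over assumed correlations of 0.3 to 0.7. The ranking does not depend on the exact value in that range, but the size of the gain does, and the documents give no correlation. The figures also assume equal variances at the two times. The clustered figures borrow the ICC given for testing. This is an improvement available at almost no cost. It does not show that the planned structural equation model is biased.

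**What to change.** In the Statistical analysis plan section:

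1. State that the MSM stigma effect is the between-arm difference in the stigma score (or latent score) at 3 and 6 months, with 6 months as the main visit, reported with a 95% CI.
2. Adjust for each man's baseline score whatever the baseline balance, and for city or any randomisation strata actually used. For this outcome, this replaces the conditional difference in differences.
3. Handle clustering consistently with the testing outcome where a facility can be assigned, and say what is done for men who attend none.
4. Say whose stigma is the mediator in the structural equation model, and keep that model as an explanatory mediation analysis.

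The cost is a few sentences and a standard model. No new data or visits are needed.

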### Sample size

Sample size calculation for MSM participants is based on testing the primary study hypothesis that multi-level intervention will increase the HIV testing rate. Our previous study showed that the 6-month HIV testing rate among MSM was 40%. We hypothesize that this rate will increase to 70% after six months of multi-level intervention. This estimate is based on the evidence from the 3MV trial which showed 81% greater odds of HIV testing in intervention compared to the control group at 6-months and is conservative in comparison to UNAIDS “90-90-90” goals. To determine whether our estimated rate of 70% following interventions is different than the comparison rate of 40% with 80% power and Type I error probability 0.05, while assuming a 10% intra-cluster correlation coefficient, we need 86 MSM participants in each arm, or 172 in two arms by the end of 6-month follow-up. Given a cohort retention rate of 80% (based on retention in previous studies with MSM in Ghana), a total of 216 MSM will be recruited. To evaluate the impact of intervention training on intersectional stigma among staff, we will test whether the training intervention will increase the willingness of HCF staff to provide services to MSM. The historical data shows that the willingness rate is 75%. We expect that the intervention will increase the willingness rate up to at least 90% in the intervention clinic staff, while there is no change in the control group, and we will need 97 staff in each arm, or 194 in total, to achieve 80% power with a 5% Type I error rate.

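### The per-protocol set excludes control men for attending facilities where testing takes place, so exclusion is tied to the outcome and the supplementary estimate can be biased in either direction

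*Protocol article*

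**What the plan says.** The outcome is defined under Outcomes: "Our primary outcome will be an uptake of HIV testing within six months of randomization".

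Step 8 (Test) directs men to facilities by arm. Intervention men are directed to an HP+ facility for testing and services. For the other arm, "the MSM in the wait-list control group will be asked to follow-up at any of the HCFs in wait-list control".

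The Statistical analysis plan section makes intention-to-treat the main approach. It then raises contamination: participants may not receive what they were randomized to, and the one example is that "some members of the control group may seek health care at the intervention HCFs during this trial". Its response is that "we will also perform per-protocol analysis, which includes only those participants who strictly adhere to the protocol", with those results reported beside intention-to-treat. Adherence is not spelled out by arm, and no crossover rate is given.

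Under Confidentiality and security of data, confirmation from a facility is sought only for men who report a test after the intervention.

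**The concern.** A per-protocol set is safest when membership does not depend on the outcome. Here the named deviation is attendance at a facility, and men are sent to facilities to be tested. Two control men with the same allocation are treated differently according to the outcome. One tests at an intervention facility, breaks the rule and leaves with outcome yes. The other never tests, cannot break the rule that way and stays with outcome no. The described facility check starts from a reported test, which tightens the link.

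The plan offers this analysis as its answer to contamination. Aim 2 is to estimate an effect size for a larger trial, so a distorted estimate printed beside the intention-to-treat result could mislead whoever designs that trial.

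**Working it through.** **Inputs from the protocol (Sample size).** The control testing rate is 40%: "Our previous study showed that the 6-month HIV testing rate among MSM was 40"%. The intervention rate is 70%: "We hypothesize that this rate will increase to 70% after six months of multi-level intervention". The evaluable number is 86 per arm: "we need 86 MSM participants in each arm, or 172 in two arms by the end of 6-month follow-up".

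**Assumed, because the protocol gives no figure.** cC and cI are the shares of control and intervention testers dropped for testing at the wrong site. cC is varied from 10% to 30%.

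**The plan's own figures.** There is no per-protocol figure to reproduce. The planned odds ratio is (0.70/0.30)/(0.40/0.60) = 3.50. The 86 is not reproduced from the stated design. A two-sided comparison of 40% with 70% at 80% power needs 42 per arm, and 86/42 = 2.05 implies about 11.5 men per cluster at an intra-cluster correlation of 0.10, a cluster size that is not stated. This matters here only because 86 is used as the arm size in step 3.

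**Step 1. Formula.** If a share c of testers is dropped and non-testers stay, a rate p becomes p(1 − c)/(1 − pc). The odds are multiplied by (1 − c), so

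per-protocol OR = full-cohort OR × (1 − cI)/(1 − cC).

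**Step 2. Only control testers dropped (cI = 0), no true effect, 40% in both arms.**

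| cC | Control rate | OR |
|---|---|---|
| 10% | 0.36/0.96 = 37.5% | 1/0.90 = 1.11 |
| 20% | 0.32/0.92 = 34.8% | 1/0.80 = 1.25 |
| 30% | 0.28/0.88 = 31.8% | 1/0.70 = 1.43 |

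These shares are 4%, 8% and 12% of all control men. At the planned 40% versus 70% with cC = 20%, the difference is 70.0 − 34.8 = 35.2 points instead of 30, and the OR is 3.50/0.80 = 4.375 instead of 3.50.

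**Step 3. False positives favouring the intervention.** In 200,000 simulated trials (86 per arm, 40% in both arms, uncorrected chi-square, no clustering), the rate was 2.6% with nothing dropped. It was 5.2%, 10.1% and 19.1% for cC = 10%, 20% and 30%.

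**Step 4. What if the excluded controls did not all test?** Drop 10% of control men, of whom a share s tested. The control rate becomes (0.40 − 0.10s)/0.90:
- s = 100%: 33.3%
- s = 60%: 37.8%
- s = 40%: 40.0%
- s = 20%: 42.2%

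The break-even point is the control average, 40%.

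**Step 5. Exclusions in the other arm, no true effect.**
- cC = cI = 20%: both rates are 34.8% and the OR is 1.00.
- cC = 10%, cI = 20%: OR = 0.80/0.90 = 0.89, against the intervention.
- cC = 20%, with 20% of intervention non-testers also dropped (for example, men who missed the retreat): the intervention rate is 0.40/(0.40 + 0.48) = 45.5% and OR = 1/(0.80 × 0.80) = 1.56.

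The size and sign therefore depend on who is dropped in each arm, and the protocol gives no figures for that.

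**The case against.** **The direction is not fixed.** A reader might infer that this analysis must favour the intervention. The documents do not support that. Intervention men are also told where to test, so strict adherence would drop those who test elsewhere, also with outcome yes. Step 5 shows that this can cancel or reverse the bias. There are reasons to expect more crossover from the control arm: nurses from intervention facilities invite men to test during a Nyansapo session, and recruitment by peer referral may link men across arms. That makes a bias toward the intervention plausible, but does not establish it.

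**The excluded controls may not all be testers.** The protocol speaks of seeking health care, which is wider than testing. That most of them tested is an inference; the bias in this arm needs only more than 40%.

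**A large spurious effect can be built, but only from assumptions.** Suppose 10% of control men cross over and all of them tested, which gives 33.3%. Suppose also that 15% of intervention men miss the retreat and test at 20%, which gives (0.40 − 0.15 × 0.20)/0.85 = 43.5%. If no intervention man tests off-site, the gap is about 10 points with no true effect. None of these inputs is in the protocol, so 10 points is not a property of the plan.

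**The target matters.** Judged against a trial without contamination, the per-protocol control rate of 34.8% at cC = 20% is too low only if more than about 35% of the crossovers would have tested anyway: (0.348 − 0.32)/0.08.

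**The definition may be left to a fuller plan.** Detail by arm can be. But this article itself fixes the strict-adherence rule and names the deviation, and that combination creates the problem.

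**The analysis is supplementary.** This stands. The primary test is by intention-to-treat, and nothing says that the per-protocol estimate will set the size of the next trial.

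**Conclusion.** The concern holds in limited form. Followed as written, the rule removes control men who test at an intervention facility and keeps control men who never test, so selection depends on the outcome. Taken alone, and assuming 10% to 30% of control testers are dropped, this turns a null odds ratio into 1.11 to 1.43. The bias in that arm requires a testing share above 40% among the excluded controls. The net direction across both arms cannot be determined from the protocol. Intention-to-treat is untouched, so the matter should be corrected but does not threaten the primary conclusion.

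**What to change.** In the Statistical analysis plan section:

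- Define per-protocol adherence by arm through receipt of the assigned components: Nyansapo and HIVE3 received in the intervention arm, not received in the control arm. State that neither whether nor where a man tested enters the definition.
- State that this set is still open to selection bias, because men who do not attend may also be less likely to test.
- State that intention-to-treat carries the conclusion and supplies the effect size for the definitive trial.
- Report facility crossover by arm as a descriptive table.

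A complier-average estimate, with random assignment as the instrument, may be added as an optional sensitivity analysis. Its exclusion restriction is strained, because assignment also directs men to HP+ facilities and so has a second path to testing. That caveat should be printed with it.

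The cost is wording only. The downside is that facility crossover is described rather than removed, so the per-protocol result no longer claims to deal with that form of contamination.
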